### Allocation

Block randomization will be used in this study. A person not involved in the execution of the trial generates the randomization list using block randomization. The same person prepares sealed envelopes containing the treatment allocation information (HTO/UKA). The block size is not revealed to the study group before analyses. The envelopes are stored in a secure place at the study center. After receiving the informed consent, a surgeon member of the study gives a sealed envelope to the patient containing the treatment allocation information, and the surgery is arranged accordingly.

### Blinding

The physical therapist will be blinded from the treatment allocation when collecting the objective measurements. The patient will be wearing long trousers during the follow-up visits and asked not to reveal the given treatment. The blinding of operative treatment is not possible for the personnel executing the operative treatment nor the patients.

### Statistical analyses

We will conduct all primary and secondary analyses according to the intention-to-treat principle. The Consolidated Standards of Reporting Trials statement will be used in the reporting of the trial results [32].

We will conduct the primary comparison (KOOS_5_ composite score) between the study groups using a mixed-model repeated-measures analysis of variance (MMRM ANOVA) allowing possible data missingness. We will assume data missing at random. Study group and time of assessment will be used as fixed factors and patients will be used as random factors. We are using the model to quantify the treatment effect as the absolute difference between the groups in KOOS_5_ (mean and 95% confidence interval [CI]) and *p*-value at 12 months postoperatively. A two-sided *p*-value of 0.05 will be used to indicate statistical significance.

We will compare secondary outcomes using a similar model where applicable (e.g., KOOS subscales, pain-VAS, Lysholm, Oxford knee score, OARSI). Radiological classification (KL- classification) is used for covariate in post hoc analysis. For categorical response variables, we will analyze the effects using the generalized estimating equations model with the unstructured correlation structure. Secondary outcomes will be considered explanatory and/or exploratory. Thus, multiplicity is not considered a problem. We will report adverse events descriptively.

We plan to perform a sensitivity analysis according to as-treated principle where the patients are analyzed according to their definitive treatment method irrespective of the randomization.

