To our knowledge, there are no previous RCTs comparing UKA with HTO in the treatment of late-stage medial knee OA. To fill this evidence gap, we designed this RCT to compare HTO and UKA in patients with medial late-stage OA of the knee with the following hypotheses.Null hypothesis is that there is no clinically significant difference between HTO and UKA in the primary outcome measure (The Knee Injury and Osteoarthritis Outcome Score composite, KOOS_5_) at 12 months postoperatively.There is no significant difference in rehabilitation time after surgery between HTO and UKA as measured with KOOS_5_ at follow-up timepoints.We expect no progression in lateral compartment OA in imaging studies during follow-up.

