### Outcomes

The outcomes of this study consist of objective and patient-reported outcomes. The outcomes will be collected at randomization, preoperative visit, and postoperatively 3, 6, and 12 months. We will follow up the participants thereafter at 2, 5, and 10 years via letter survey.

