#### Primary outcome measure

The Knee Injury and Osteoarthritis Outcome Score (KOOS) is a validated patient-reported outcome measure (PROM) assessing the outcomes of various knee conditions [22]. The tool consists of five subscales: pain, other symptoms, activities of daily living, function in sports or recreational activities, and quality of life. We will use the KOOS_5_ composite score as the primary outcome measure. Based on clinical experience and literature, there will be only minimal change in pain and PROM scores after 1 year postoperatively [23]. Thus, the primary outcome measure, KOOS_5_ score for HTO vs. UKA is analyzed 12 months postoperatively. A minimal clinically important difference (MCID) of 10 points will be used [24].

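### The terms listed for the primary model omit the group-by-time interaction that the stated 12-month difference requires

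*Protocol article*

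**What the plan says.** Under Statistical analyses, the protocol article plans the primary comparison of KOOS5 "using a mixed-model repeated-measures analysis of variance (MMRM ANOVA) allowing possible data missingness". It gives the terms in one sentence: "Study group and time of assessment will be used as fixed factors and patients will be used as random factors". The next sentence begins "We are using the model to quantify the treatment effect as the absolute difference between the groups" and ends by fixing that difference, with its 95% confidence interval and p-value, at 12 months after surgery. The same section applies a similar model to the KOOS subscales, pain VAS, Lysholm, Oxford knee score and OARSI tests.

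The 12-month target is repeated under Primary outcome measure: "Thus, the primary outcome measure, KOOS_5_ score for HTO vs. UKA is analyzed 12 months postoperatively". The schedule under Outcomes is wider: "The outcomes will be collected at randomization, preoperative visit, and postoperatively 3, 6, and 12 months". The article does not say which of these five visits supply responses to the model and which, if any, supply a covariate. The second hypothesis in the Introduction concerns the course of recovery: "There is no significant difference in rehabilitation time after surgery between HTO and UKA as measured with KOOS_5_ at follow-up timepoints".

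**The concern.** A model with group, time and a random patient effect has a single group coefficient. It has no parameter for the difference at a particular visit. To obtain a 12-month difference from a repeated-measures model, the group effect must be allowed to vary by visit, which is what the group-by-time interaction does. The listed terms and the stated estimate therefore do not fit together.

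The gap concerns the primary test. An analyst could follow the listed terms to the letter, report the common coefficient as the 12-month result, and be in line with the published text. Another could add the interaction, report the 12-month contrast, and also be in line with it. If the HTO-UKA difference changes during recovery, the two could reach different conclusions. The protocol does not take a constant difference as given, because its second hypothesis compares the groups at the separate follow-up timepoints.

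**Working it through.** **Inputs from the protocol article.** Difference 10 points, SD 15, two-sided alpha 0.05, 80% power and 36 per group (Sample size); visits at randomization, before surgery, and at 3, 6 and 12 months (Outcomes).

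**Assumed, because the article does not give them.** Within-patient correlation ρ of 0.3 to 0.7, equal between all visits; complete data; the visit profiles of the true difference shown below.

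**Step 1: the plan's own figure.** For a comparison at one timepoint, n = 2 × (1.96 + 0.842)² × 15² / 10² = 35.3, so 36 per group. The standard error (SE) is 15 × √(2/36) = 3.54 and the normal-approximation power is 80.7% (79.7% with the noncentral t). The 36 per group is reproduced, and it is a single-timepoint calculation.

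**Step 2: what the listed terms estimate.** With k modelled visits, balanced data and equal correlation, the group coefficient of group + time + random patient is the simple mean of the k visit-specific differences. Its standard error is

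SE = 15 × √((1 + (k − 1)ρ)/k) × √(2/36).

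- k = 3: 2.58 at ρ = 0.3, 2.89 at 0.5, 3.16 at 0.7.
- k = 5: 2.35 at ρ = 0.3, 2.74 at 0.5, 3.08 at 0.7.

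The rejection probability is Φ(|estimate|/SE − 1.96) + Φ(−|estimate|/SE − 1.96).

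**Step 3: results under the assumed profiles.**

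| True differences by modelled visit | True 12-month difference | Expected estimate | Rejection probability, ρ = 0.3 / 0.5 / 0.7 |
|---|---|---|---|
| 3, 6, 12 months: 10, 5, 0 | 0 | 15/3 = 5.0 | 49% / 41% / 35% |
| 3, 6, 12 months: 0, 5, 10 | 10 | 15/3 = 5.0 | 49% / 41% / 35% |
| Two pre-operative visits, then 3, 6, 12 months: 0, 0, 10, 10, 10 | 10 | 30/5 = 6.0 | 73% / 59% / about 50% |
| 3, 6, 12 months: 10, 10, 10 | 10 | 30/3 = 10.0 | 97% / 93% / 89% |

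In the first row, any rejection is a false positive for the 12-month question, where the nominal rate is 5%. The third row applies only if both pre-operative scores are responses; randomization makes the expected difference at those visits zero. The last row shows no bias.

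**Step 4: check with fitted mixed models.** Sixty simulated trials per profile, 36 per group, ρ = 0.5:

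| Profile | Mean estimate, group + time | Mean 12-month contrast, group x time |
|---|---|---|
| 0, 5, 10 | 5.2 | 10.2 |
| 10, 5, 0 | 4.7 | 0.0 |
| 0, 0, 10, 10, 10 | 6.5 | 10.5 |

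The additive fits agree with Step 2 within simulation error, and the interaction model recovers the 12-month truth. The standard error of its 12-month contrast was about 3.5, in line with the 3.54 of Step 1. The planned sample size thus belongs to the 12-month contrast and not to the common coefficient.

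**The case against.** The strongest reply is that the sentence names the factors of a repeated-measures ANOVA and does not claim to list every term. Naming two fixed factors does not exclude their interaction, and nowhere does the article call the model additive or the reported effect an average over visits. The sentence that follows asks for a 12-month difference, and the second hypothesis compares the groups at separate timepoints; both suggest that a visit-specific contrast was intended. A journal article also condenses a full protocol and may leave model terms to an analysis plan that is not shown.

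Much of this stands. A reader might infer that the primary model definitely has main effects only, and hence that the primary estimate and its type I error are wrong. The documents do not support that: it turns an unnamed term into an excluded one. It also needs a difference that varies over the modelled visits, and no passage supplies such a profile. Nor does the article say that pre-operative scores are responses, so the figure of 6.0 is doubly conditional.

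What does not stand is that nothing needs doing. The article is not silent on the model: it lists terms and says that this model yields the 12-month estimate, and fitted as listed those terms do not. If the interaction is intended, one sentence settles it.

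**Conclusion.** The point holds as a gap in a stated specification that bears on the primary test. The terms as listed do not yield the estimate attributed to them. Whether the reported result would be biased depends on two further conditions: that the model is fitted without the interaction, and that the difference is not constant over the visits entered. Where both hold, the error can be of clinical size against the protocol's 10-point threshold: 5.0 points in either direction under the assumed 10/5/0 and 0/5/10 profiles, and 4.0 points (10 − 6.0) with both pre-operative scores as responses. Where the difference is constant and only post-operative visits are modelled, there is no bias. The profiles, the correlation range, the complete data and the role of the pre-operative scores are assumptions. The conclusion that the interaction should be named rests on none of them.

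**What to change.** Amend the model description to: fixed effects of study group, visit and group x visit, with patient as a random factor; the primary estimate is the model-based HTO-UKA contrast in KOOS5 at 12 months, with 95% confidence interval and two-sided p-value. State whether KOOS5 at randomization and at the preoperative visit enters as a response or as a covariate. Use the same form for the secondary outcomes analysed with the similar model; the visit-specific contrasts then also serve the second hypothesis. Limiting responses to post-operative visits, or changing the covariance structure, is not needed to close this gap.

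The interaction adds k − 1 fixed parameters: 2 with three modelled visits, 4 with five. The 12-month contrast gives up the smaller standard error of an average over visits (2.58 to 3.16 for three visits, against about 3.54), but the sample size never relied on that gain, so the basis of 36 per group does not change. Under Trial status the article describes the trial as still to start, so the wording could be settled ahead of any outcome data; at the latest it should be settled before the primary analysis.

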#### Baseline data

Baseline data is collected at the time of randomization at the outpatient clinic. These include radiographs of the affected knee, weight-bearing mechanical axis, MRI, KOOS_5,_ Lysholm, Oxford knee score, and Osteoarthritis Research Society International (OARSI) performance-based measures. The patients receive an activity watch (Withings Move®, Issy-les-Moulineaux, France), which they are asked to use day and night throughout the trial.

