**Primary outcome measure**
1. KOOS_5_ at 12 months postoperatively

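### The primary model does not name baseline KOOS5 as a covariate, so the 12-month comparison stays unbiased but gives up precision that data already collected could supply

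*Protocol article*

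**What the plan says.** The primary endpoint is "KOOS_5_ at 12 months postoperatively" (Outcomes, Table 3). The Statistical analyses section plans a mixed model for repeated measures, with these terms: "Study group and time of assessment will be used as fixed factors and patients will be used as random factors". The model is used to "quantify the treatment effect as the absolute difference between the groups in KOOS_5" at 12 months, with a 95% confidence interval and a two-sided test at 0.05.

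Baseline KOOS5 will be available. The Baseline data section says "Baseline data is collected at the time of randomization at the outpatient clinic" and then "These include radiographs of the affected knee, weight-bearing mechanical axis, MRI, KOOS_5,_ Lysholm, Oxford knee score". The Outcomes section gives the full schedule: "The outcomes will be collected at randomization, preoperative visit, and postoperatively 3, 6, and 12 months".

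The only covariate named anywhere is Kellgren-Lawrence grade, and only for a later analysis: "Radiological classification (KL- classification) is used for covariate in post hoc analysis". The Sample size section uses a difference of 10 points, an SD of 15, two-sided 5% error and 80% power. It arrives at 36 per group, raised to 50 for an assumed 36% loss. The Allocation section describes block randomization and mentions no stratification.

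**The concern.** A patient's score before surgery usually predicts the score a year later. If it does so here, part of the between-patient spread in the 12-month scores is already explained by data in hand. A model that leaves baseline out treats that part as noise, so the confidence interval is wider and the power lower than they need be.

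The article lists the model's terms and says where its single covariate will be used. Leaving out baseline KOOS5 is therefore a feature of the model as stated. At stake is how precisely a trial of 100 patients can estimate a difference it regards as important at 10 points, when it expects to lose a sizeable share of its patients.

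**Working it through.** **Inputs.** Difference 10, SD 15, two-sided 0.05, 80% power, 36 per group, 50 randomized per group and 36% loss come from the Sample size section. The baseline to 12-month correlation r is not in the document; it is assumed to be 0.3 to 0.6, with 0.2 shown as a low case.

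**Step 1: reproduce the plan's figure.** n = 2 × (1.96 + 0.8416)² × 15² / 10² = 35.3, so 36 per group, as stated. The noncentral t gives 79.7% power at 36. The figure comes from the raw SD, with no baseline correlation.

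**Step 2: patients left under the plan's own loss rate.** 50 × (1 − 0.36) = 32 per arm.

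**Step 3: effect of adjustment.** Residual SD = 15 × √(1 − r²). SE of the 12-month difference = residual SD × √(2/n). Power is from the noncentral t with noncentrality 10/SE and one further degree of freedom spent on the covariate.

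| r (assumed) | Residual SD | Variance cut | 95% CI half-width, 36 per arm | Power, 36 per arm | Power, 32 per arm |
|---|---|---|---|---|---|
| none (unadjusted) | 15.00 | – | 7.05 | 79.7% | 74.7% |
| 0.2 | 14.70 | 4% | 6.91 | 81.2% | 76.4% |
| 0.3 | 14.31 | 9% | 6.73 | 83.2% | 78.6% |
| 0.4 | 13.75 | 16% | 6.46 | 86.1% | 81.7% |
| 0.5 | 12.99 | 25% | 6.11 | 89.6% | 85.8% |
| 0.6 | 12.00 | 36% | 5.64 | 93.6% | 90.7% |

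Put differently, at r = 0.5 the 36 patients per arm carry the information of 36/0.75 = 48.

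**Step 4: does entering baseline as a time level recover this?** In 20,000 simulated trials (36 per arm, complete data, equal correlation r between visits), baseline was one level of time, with a separate mean for each group at each visit. The 12-month contrast is then the raw mean difference. At r = 0.5 its SE was 3.53, against 3.07 with baseline as a covariate; at r = 0.3 the SEs were 3.54 and 3.40. So entering baseline as a response without an equal-means constraint gains nothing. If baseline were a level and no group-by-time term were fitted, the group effect would average over visits: (0 + 10 + 10 + 10)/4 = 7.5 instead of 10, as the simulation also gave.

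**Step 5: chance imbalance at baseline.** Assume a baseline SD of 15 as well. With 36 per arm, SE = 15 × √(2/36) = 3.54 and P(difference of 4 or more points) = 2 × P(Z > 4/3.54) = 0.26. With 50 per arm, SE = 15 × √(2/50) = 3.0 and the probability is 2 × P(Z > 4/3) = 0.18. With equal SDs, about r times the difference carries into the 12-month estimate: for 4 points, 0.3 × 4 = 1.2 to 0.6 × 4 = 2.4 points.

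**The case against.** The best defence is that a journal article condenses the full plan. The quoted sentence speaks of factors, which in analysis-of-variance language are categorical, so a continuous baseline score might not be listed there. It also names no group-by-time term, although an effect at 12 months is promised, so it is plainly not a full specification. This has some force: one cannot infer that an unseen analysis plan rules baseline out. But the article does set out the model's terms and does say where its one covariate is used, and on that text the 12-month comparison is unadjusted.

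A second defence is that baseline may already be in the model as a level of time, since KOOS5 is collected at randomization. The text leaves this open. It would recover most of the precision only if the groups were constrained to a common baseline mean, and no such constraint is described.

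Third, the gain rests on an assumed r. That stands: at r = 0.2 it is under 2 percentage points of power.

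A reader might also infer that a baseline imbalance of several points is likely and would bias the result. The figures do not support that. A difference of 4 or more points has about a 26% chance with 36 per arm, only a fraction of it carries over, and the unadjusted interval already allows for it. It is the same loss of precision seen from another side. Nor should the point be argued from the chance that the interval falls within ±10: the trial is described as a superiority trial tested at 0.05, and 10 points is its minimal clinically important difference, not a decision margin.

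**Conclusion.** The point holds as a loss of efficiency, not of validity. As stated, the primary model makes no use of baseline KOOS5 that would improve precision at 12 months, although the score is collected. For r between 0.3 and 0.6, this forgoes about 3 to 14 percentage points of power with 36 per arm (79.7% against 83.2% to 93.6%), and about 4 to 16 points with 32 per arm (74.7% against 78.6% to 90.7%).

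These figures rest on the plan's SD of 15 and difference of 10, a linear relation of equal strength in both arms, and an r that the document does not supply. The fall from 36 to 32 evaluable patients is a separate sample-size matter; here it only shows where the extra precision would be most useful. The change should be made because it costs almost nothing, but the trial's conclusion would not be invalid without it.

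**What to change.** Before any unblinded analysis, state that the primary model takes the 3, 6 and 12 month KOOS5 scores as responses. Its fixed effects should be group, visit, group-by-visit, randomization-visit KOOS5 and baseline-by-visit, and the treatment effect should be read from the 12-month contrast. Equivalently, keep baseline among the responses and constrain the two groups to a common baseline mean. Either wording also settles baseline's role and supplies the group-by-visit term.

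Use the randomization visit, not the preoperative visit, as baseline, because the latter comes after patients know their allocation. For the same reason, confirm that KOOS5 is completed before the envelope is opened: the Implementation section mentions the baseline measures after that step.

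Apply the same form to continuous secondary outcomes that have a baseline score. Keep the sample size unchanged and treat the gain as a reserve. The cost is one line of wording and the ClinicalTrials.gov update that the Protocol amendments section already requires. No new data, visits or patients are needed.

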### Data monitoring

Data monitoring committee, interim analyses, or stopping guidelines are not included in this study because both operative treatment options are already in daily practice and the results have been acceptable.

### Harms

All complications and harms are reported in the results section of this study. Major and minor complications are listed in the safety consideration section.

### Protocol amendments

In the case of modification of the study protocol, all changes will be updated to ClinicalTrials.gov.

### Confidentiality

Trial data will be stored in a secure storage at the study center for 10 years after the completion of the study. All data will be handled according to the principles of the GDPR.

### Participant timeline

The participant timeline is represented in Table 2 and the flow chart is in Fig. 1.

**Fig. 1 Fig1:**
[figure not shown]
Study flow chart

### Implementation

The recruitment is done by the surgeon member of the study. After receiving the written consent, the surgeon member opens the envelope, and the patient is then randomized to one of the study groups. A physical therapist does the baseline measures, and the patient receives a written guide for exercise therapy.

### Secondary cohort study

Eligible patients declining randomization are offered to participate in a concurrent observational cohort (“declined cohort”). In addition, patients who are ineligible for the RCT but are treated with either UKA or HTO are asked to take part in a second cohort study (“ineligible cohort”). Those consenting to these cohorts can choose their preferred treatment method after information on both treatment methods is given. Both cohorts are followed up according to the same principles as the participants of the RCT. The results of the declined and ineligible cohorts will be analyzed separately from the RCT.

### Data collection and management

The data is collected by the physical therapist and research nurse using paper forms. The original paper forms are evaluated visually, and missing data is acquired if possible. From the paper forms the data is secured in an electronic archive. Only the research nurse is allowed to access the data during data gathering. In case of missing items in the master data, the original paper forms are reassessed and if needed the patient is contacted.

